Studies demonstrating relationships between trans-fat intake and cancer in childhood are lacking. However, evidence has shown some possible negative effects on other health outcomes among children. Bouwstra and colleagues have shown that neonates with high TFA umbilical levels have a less favorable neurologic condition at 18 months [27]. Furthermore, a recent review (including human and animal studies) concluded that fetal exposure to trans-fat appears to increase the offspring risk for developing metabolic diseases throughout life [28]. TFAs also interfere in the metabolism of long-chain polyunsaturated fatty acids which might result in a negative impact on infant growth and development [29, 30]. Lifelong, including prenatal, consumption of a diet rich in polyunsaturated fatty acids (PUFA, contained in nuts, seeds and fish) has been shown to protect against tumor growth and to modify glucose metabolism in Walker tumor cells and lymphocytes in Wistar rats [31]. Therefore, the inhibitory effect of PUFA and their interference with trans fatty acids might also be relevant in the fetal programming of childhood cancers.

Despite a general reduction in the iTFA use in food production, Denmark, as the first EU country, legislated against the use of iTFA in all Danish and imported human foodstuffs [32]. The order came into effect on March 31st, 2003, with a transition period until January 1st, 2004. The order imposed a maximum of 2 g of iTFA/100 g oils and fats. During the transition period a maximum level of 5% iTFA was allowed in foodstuffs also containing ingredients other than oils and fats [32]. This legislation led to a radical reduction of iTFA from margarine and shortenings which resulted in a rapid decline in products with trans-fat followed by a decrease in population-level CVD mortality rates [33].

Despite the alarming evidence of increased risk of several diseases caused by TFA consumption and the fact that millions of people still have a too high iTFA intake in Europe, currently no EU legislation regulates the content of iTFA in food products [34].

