### Hypotheses and objectives

We hypothesize that high TFA exposures, and in particular iTFA exposures, during the critical phase of fetal development increase the risk of developing childhood cancers in general and haematopoietic neoplasms in particular.

We investigate this in two broad designs and study objectives:We will examine if the legislatively reduced use of iTFA in the production of human foodstuff for the Danish market has shown any beneficial effect on population level in preventing childhood haematopoietic neoplasms. Thus we will compare the incidence of childhood haematopoietic neoplasms between all Danish children born in the years before and after the law came into effect. The specific hypothesis is that individuals born in 2004–2008 were exposed to reduced iTFA during fetal development and will have a lower risk of developing childhood haematopoietic neoplasms compared to individuals born in 1988–2003, before the policy was implemented, while taking into account the underlying secular trends in these cancers.We aim to compare neonatal levels of TFA in children with and without a later diagnosis of childhood haematopoietic neoplasm in a matched case-control study. As a secondary aim, we wish to investigate the interactions between TFA and polyunsaturated fatty acids, and their impact on risk of haematopoietic neoplasms in children, since TFA have been shown to inhibit the metabolism of polyunsaturated fatty acids.

The aim of this protocol is to describe the methods and analyses that will be used in this study to investigate the influence of prenatal exposure to trans-fatty acids for development of haematopoietic neoplasms (EnTrance). If deviations from this initial study protocol occur during data analyses, we will update the protocol.

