**Fig. 1 Fig1:**

Constitution of the exposed versus non-exposed groups of cases who developed haematological malignancy before the age of 7 years and registered in The Danish Cancer Registry (Objective 1)

The incidence of childhood haematopoietic neoplasms among 1,101,055 individuals from the period before the iTFA legislation born between January 1st, 1988 and August 31st, 2004, will be compared to the incidence of childhood haematopoietic neoplasms among 276,422 individuals from the period after the iTFA legislations born between September 1st, 2004 and December 31st, 2008, as a proxy of iTFA gestationally exposed or not exposed, respecitvely. In this overall time period approximately 740 incident haematopoietic neoplasms cases occurred in children before the age of 7 years.

*The second objective* is a case-control study investigating biomarkers of neonatal trans-fatty acid concentrations from stored DBS [34] from individuals who developed childhood haematopoietic neoplasms before the age of 7 years and born in the period 1988–2008 compared to matched controls (Fig. 2).

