### Statistical analysis

In objective 1 we will use a Cox proportional hazard model with age as the underlying timescale to investigate the hazard of childhood haematopoietic neoplasms in children born before and after the iTFA ban, as a proxy for iTFA exposed or not exposed in fetal life. Observations will be censored in case of death, immigration or at 7 years of age. To take the potential secular trend in the incidence of haematopoietic neoplasms into account we will model the variation in cancer risk across birth cohorts by a piecewise linear spline with a knot at 1st of September 2004. Further, we will investigate incidence trends over time.

By examining *all* children from the entire national birth cohorts it is reasonable to assume that all confounding variables will be equally distributed among the exposed and non-exposed individuals, but still we will investigate potential influence of secular variation or possible confounding effects which might have changed during the time period and which might be associated with both TFA exposure and haematopoietic neoplasms. Such potential confounders could be age of the mother at the time of giving birth, assuming accumulation of TFA with age and an older age for first time pregnancies over time. The median gestational age might have increased during the investigated time period, which would increase the average intrauterine exposure to TFA over the study period [44]. Smoking status during pregnancy might have decreased over time and smoking might be associated with increased cancer risk, smoking is also associated with gestational age and thereby with the length of the TFA exposure during pregnancy.

As sub-analysis we will exclude cancer cases diagnosed before the 90 day of life since the origin most likely is due to chromosomal alterations leading to oncogene activation [37]. If feasible we will investigate the first born only since some studies have shown higher risk of childhood cancers in the first born compared to their younger siblings [45] and sensitivity analysis of sub-types of haematopoietic neoplasms (leukemia and lymphoma). Further, we will investigate children with early diagnosis, e.g. before age 4 years.

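### Objective 1: the secular-trend spline has its only knot at the exposure cut and no term is named as the ban effect, so neither reading of the model gives the powered before/after hazard ratio

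*Protocol article*

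**What the plan says.** The Statistical analysis section sets up a Cox model on the age scale "to investigate the hazard of childhood haematopoietic neoplasms in children born before and after the iTFA ban"; birth period stands in for fetal exposure. The next step is an adjustment for a possible trend in incidence, worded as follows: "we will model the variation in cancer risk across birth cohorts by a piecewise linear spline with a knot at 1st of September 2004". The section does not say whether a before/after indicator stands in the same model as the spline, or which coefficient is the estimate of the ban effect.

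Other sections fix the target:

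- Hypotheses and objectives: children born after the policy "will have a lower risk of developing childhood haematopoietic neoplasms compared to individuals born in 1988–2003, before the policy was implemented", with secular trend taken into account. The years there are 2004–2008 against 1988–2003.
- Study population, text at Fig. 1: the groups are "1,101,055 individuals from the period before the iTFA legislation born between January 1st, 1988 and August 31st, 2004" and "276,422 individuals from the period after the iTFA legislations born between September 1st, 2004 and December 31st, 2008". The cut is therefore the spline's knot date. About 740 cases before age 7 are expected overall.
- Power calculation: one exposed-versus-unexposed HR of 1.35, at 80% power and 5% significance, from a two-group log-rank calculation.
- Background: "This legislation led to a radical reduction of iTFA from margarine and shortenings which resulted in a rapid decline in products with trans-fat".

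**The concern.** The hypothesis, the group definition and the power statement all describe one contrast of level between two birth periods, adjusted for trend. A trend term that may bend exactly where exposure changes competes with that contrast. A linear spline in its usual sense is continuous at its knot, so on its own it has no parameter for a step there. With an indicator beside it, the change after the ban is divided between a jump at the knot and a new slope, and the indicator carries only the jump.

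Three quantities could then be reported as the ban effect: the jump, the slope change, or the average post-ban departure from the earlier trend. They differ in meaning and in precision, and the power statement covers none of them. A null result could be read as evidence against an effect of the size the study claims it can detect, when the coefficient reported had about one chance in three of detecting it.

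**Working it through.** **Inputs.** From the article: 1,101,055 births before the cut (1 January 1988 to 31 August 2004, 200 months), 276,422 after it (1 September 2004 to 31 December 2008, 52 months), about 740 events, 5% significance, 80% power, HR 1.35. Assumed: two-sided test, births spread evenly within each period, complete follow-up to age 7, and incidence flat apart from any ban effect.

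**The plan's own figure.** The post-ban share is p = 276,422 / 1,377,477 = 0.2007. With no trend term, the standard error of the log HR is 1/√(740 × 0.2007 × 0.7993) = 0.0918. The least detectable HR is exp[(1.960 + 0.842) × 0.0918] = 1.29 by Schoenfeld's formula. Freedman's formula, with the pre-ban group as exposed, gives 1.32. With 700 events the two are 1.30 and 1.34. The stated 1.35 is not reproduced exactly, but it errs slightly on the cautious side for a two-group test without trend. That test is not the planned analysis.

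**Candidate models.** I fitted expected-count Poisson models to the 252 monthly birth cohorts, as a stand-in for the Cox model. With t in years from the cut, the candidate terms are t, max(t, 0) for the bend, and a post-ban indicator. The standard error and least detectable HR are under no effect. The power is at a true post/pre HR of 1/1.35 = 0.741 (log HR −0.300), using the standard error under that alternative.

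| Model and coefficient tested | SE, no effect | Least detectable HR | Power at 1.35 |
|---|---|---|---|
| Indicator, no trend | 0.092 | 1.29 | 84% |
| Indicator + one linear trend: indicator | 0.128 | 1.43 | 61% |
| Indicator + spline: jump at the knot | 0.184 | 1.67 | 32% |
| Indicator + spline: average post-ban HR against extrapolated pre-ban trend | 0.128 | 1.43 | 61% |
| Spline only: slope change | 0.046 per year | no step parameter | 38% |

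**Check on the second row.** The squared correlation of t with the indicator, weighted by births, is 0.484, so the standard error is 0.0918/√(1 − 0.484) = 0.128.

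**Spline only.** With a true step to 0.741, the fit gives a slope change of −0.0831 per year (SE 0.0502, z = −1.66). Power is Φ(1.655 − 1.960) = 38%. The fitted departure from the extrapolated pre-ban trend is 1.00 at the cut, exp(−0.0831 × 2.167) = 0.835 on average (2.167 years is the mid-point of the 4.33-year post-ban period), and exp(−0.0831 × 4.333) = 0.70 at the end of 2008. The pre-ban slope is −0.0046 per year, a spurious decline of about 7% over 16.67 years.

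**Indicator plus spline.** The jump is recovered at 0.741 without bias, with SE 0.202 under this alternative. Power is Φ(0.300/0.202 − 1.960) = 32%.

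**Where the loss arises.** Adjusting for any linear trend takes power from 84% to 61%. Reporting only the jump in a model that also bends at the cut takes it from 61% to 32%. Against the one-trend model the variance ratio is (0.184/0.128)² = 2.1 under no effect and (0.202/0.133)² = 2.3 under the alternative.

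**The case against.** The section names the before/after contrast first and brings in the spline as trend adjustment, so an indicator plus a spline is a natural reading. That stands. A reader might infer that the planned model cannot represent a before/after step at all. The text supports this only if the spline is the whole model, and it does not say so. With an indicator present the step is estimated without bias.

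A reader might also attribute a fourfold variance to the knot. That ratio, (0.184/0.092)², is against a model with no trend, which the hypothesis itself excludes; the fair ratio is 2.1 to 2.3. Nor is it right that the spline mainly hides the ban effect as earlier secular decline. Even in the spline-only fit, most of the step goes into the post-ban slope and only about 0.5% a year into the pre-ban trend.

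A slope change at the intervention date is a standard interrupted-time-series choice. The article gives reasons to expect a gradual effect: a general reduction in use, the 2003 transition period, and maternal adipose stores. This is a fair argument for keeping a slope-change model, but not for leaving the reported contrast open. A level-and-slope model gives a usable average effect with SE 0.128.

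Lastly, this is a condensed article, calls the study explorative, and may leave the reported coefficient to a fuller plan. Silence on that alone would not be a finding. The knot, however, is stated, and its position changes the estimand or costs about half the power whichever way the sentence is read.

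**Conclusion.** The concern holds in a limited form. The stated trend term has its only knot at the exposure cut, and neither reading of the model yields the single before/after HR of the hypothesis at the stated sensitivity. The spline alone tests a slope change, with about 38% power against a true step of 0.74 and an average effect shown as about 0.84. The indicator plus spline gives an unbiased jump, with a least detectable HR of about 1.67 and about 32% power at 1.35. Even a well-specified trend adjustment gives about 1.43, so 1.35 is too favourable for any trend-adjusted contrast examined here except as a two-group figure.

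The sizes rest on 740 events, even births within each period, flat underlying incidence, a two-sided 5% test and, for the power figures, a clean step at 1 September 2004. A gradual effect would change them, and would move part of the effect from the jump into the slope.

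**What to change.** Write out the main objective 1 model and name the reported coefficient, in one of two ways:

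1. A Cox model with a post-ban indicator plus one linear birth-date trend that has no knot at the cut; report the indicator HR.
2. A Cox model with level and slope change; report the average post-ban HR against the extrapolated pre-ban trend.

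Keep the continuous spline and the separate-slope model as sensitivity analyses. Restate the least detectable HR for the trend-adjusted contrast, about 1.43 under the assumptions above.

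The change is to wording and one power figure; no data collection is affected. It has two costs. The first option assumes that the secular slope does not change at the ban, which the sensitivity models examine. The stated detectable HR also becomes less favourable.

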Conditional logistic regression analyses will be used in the 2nd objective to compare blood spot fatty acid levels between subjects with haematopoietic neoplasms and matched subjects who have not developed cancer. We will investigate industrial as well as ruminant TFA independently and mutually adjusted. Based on a priori consideration we will adjust for maternal and paternal age, smoking during pregnancy, birth weight and gestational age. Also, there might be regional and urban/rural differences in iTFA intake. Place of residence is available from Statistics Denmark, and can be included into analyses. Diets are usually different between families with higher and lower socioeconomic status and maternal socioeconomic status may influence intake of certain food products rich in trans-fat. Information on socioeconomic status, education and ethnicity is available from Statistics Denmark and can be controlled for.

As mentioned in the methods description, other fatty acids potentially related to haematopoietic neoplasms in children will be analysed in the DBS since our methodology allows a complete separation, identification and quantification of sixty fatty acids. We will therefore also investigate interactions between TFA and polyunsaturated fatty acids, and risk of haematopoietic neoplasms in children as well as association between polyunsaturated fatty acids and risk of cancer stratified by trans fatty acids.

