Other health outcomes in children, which will not be described in this protocol, will be investigated in future studies using the same study designs, include: negative birth outcomes, cognitive function, epilepsy, asthma, heart disease, eye diseases, bone fracture, and metabolic diseases like type 1 diabetes and childhood obesity.

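### Objective 2 fixes birth weight as a covariate although it may lie on the pathway from prenatal TFA to cancer, so the odds ratio may not estimate the effect hypothesised

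*Protocol article*

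**What the plan says.** The Statistical analysis section sets the model for objective 2: "Conditional logistic regression analyses will be used in the 2nd objective to compare blood spot fatty acid levels" between cases and matched controls. It then fixes the covariates a priori: "we will adjust for maternal and paternal age, smoking during pregnancy, birth weight and gestational age". Neither birth weight nor gestational age is given a rationale in that paragraph. Place of residence, socioeconomic status, education and ethnicity appear there only as factors that could be added.

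The target is stated under Hypotheses and objectives: the team hypothesises that "high TFA exposures, and in particular iTFA exposures, during the critical phase of fetal development increase the risk of developing childhood cancers". Nothing there restricts the question to the part of the effect that bypasses fetal growth.

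Two places bear on birth weight as a possible result of exposure. The Background says that TFA interferes with fatty acid metabolism, "which might result in a negative impact on infant growth and development". The Discussion says that other child health outcomes "will be investigated in future studies using the same study designs, include: negative birth outcomes".

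Gestational age has a different role. Among the potential confounders for objective 1, the Statistical analysis section says: "The median gestational age might have increased during the investigated time period, which would increase the average intrauterine exposure to TFA" and "smoking is also associated with gestational age and thereby with the length of the TFA exposure during pregnancy".

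**The concern.** A variable that the exposure can change is not an ordinary confounder. If prenatal TFA affects fetal growth, and birth weight is related to haematopoietic neoplasms, then conditioning on birth weight blocks that route. The odds ratio is then closer to a direct effect than to the effect of prenatal exposure as a whole. If birth weight also shares unmeasured causes with these cancers, conditioning on it can open a non-causal path as well.

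What is at stake is the meaning of the objective 2 estimate. The article says that the two objectives reinforce each other. Objective 1 contrasts births before and after the ban, and its named confounders do not include birth weight. Adjusting for it only in objective 2 could leave the two estimates answering different questions.

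**Working it through.** **1. The plan's own figure.** The Power calculation section gives a least detectable odds ratio of 1.35 to 1.75 for 700 cases and 700 controls, 80% power and control exposure of 10–90%. The significance level (5%) is stated only for objective 1. I assumed two-sided 0.05 and no case-control correlation in exposure.

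With control exposure p0, let p1 = p0·OR / (1 + p0(OR − 1)), d10 = p1(1 − p0) and d01 = (1 − p1)p0. Power is Φ[(√700·|d10 − d01| − 1.96·√(d10 + d01)) / √(d10 + d01 − (d10 − d01)²)]. Solving for 80% power:

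| Control exposure | Least detectable OR |
|---|---|
| 10% | 1.583 |
| 30% | 1.375 |
| 50% | 1.352 |
| 70% | 1.405 |
| 90% | 1.760 |

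The stated range is reproduced. The point does not depend on it; 1.35 serves below only as a convenient total effect.

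**2. What the article supports for each link.**

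| Link | Birth weight | Gestational age |
|---|---|---|
| Possible effect of TFA | Inferred from infant growth (Background) and adverse birth outcomes (Discussion); not named | Only through the general mention of birth outcomes |
| Determinant of exposure | Not stated | Stated: it sets the length and amount of exposure |
| Effect on cancer risk | Not stated | Not asserted; discussed among potential confounders |

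The blood spot is taken 48–72 h after birth and is read as reflecting the mother's TFA status at the end of pregnancy (Study population). Both variables are therefore settled before the biomarker is measured, while the exposure it stands for acts earlier.

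**3. Illustration of direction and size.** The article gives neither path strength, so everything here is assumed. For a rare outcome without interaction, with a = change in birth weight (SD) per SD of TFA and g = cancer odds ratio per SD of birth weight:

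ln(adjusted OR) = ln(total OR) − a·ln(g)

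Take a total OR of 1.35 per SD, so ln 1.35 = 0.3001, and a between −0.05 and −0.30 (TFA lowers birth weight).

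- g = 1.00: a·ln(g) = 0, and the adjusted OR is 1.35. Nothing changes.
- g = 1.10, a = −0.20: adjusted OR = 1.376.
- g = 1.20, a = −0.30: a·ln(g) = −0.30 × 0.1823 = −0.0547, so the adjusted OR is exp(0.3001 + 0.0547) = 1.43. The log OR moves by 0.0547 / 0.3001 = 18%, away from the null.
- g = 1/1.20, a = −0.30: a·ln(g) = +0.0547, so the adjusted OR is exp(0.3001 − 0.0547) = 1.28. The log OR moves by the same 18%, towards the null.

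The sign of the change depends on whether higher birth weight raises or lowers cancer risk, which the article does not say.

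**The case against.** The strongest reply concerns gestational age. A reader might infer that the article treats both birth variables as effects of TFA and that both should leave the model. The text does not support that. It places gestational age upstream, as a determinant of how long the fetus is exposed, and discusses it among potential confounders. It is also fixed when the blood spot is taken and may influence the measured level. On the article's own reasoning, adjusting for it is confounder control. This part of the objection stands.

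Second, birth weight is never named as an effect of TFA, and listing birth outcomes for later study does not assert an effect. That is correct, and it is why the point says that birth weight may lie on the pathway. The inference is still fair: birth weight is a natural measure of both growth and birth outcome.

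Third, a reader might infer that adjustment removes part of the effect and makes a false null more likely. That needs a link from birth weight to cancer of a particular sign, and the article asserts none. The illustration moves either way. The collider argument likewise needs shared causes that the article does not mention. This part also stands.

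Fourth, a journal article condenses the plan, so model sequences and covariate rationale may be given elsewhere, and the Discussion says that the linked data allow mediation to be studied. Missing detail is indeed no fault here. But the inclusion of birth weight is a stated, a priori choice, and no mediation analysis is described that would make it a direct-effect model.

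Finally, birth weight might act as a proxy for unmeasured confounding. That is possible, but the article does not argue it.

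**Conclusion.** The point holds for birth weight. It is a fixed covariate without a stated reason, the hypothesis concerns the effect of fetal exposure as a whole, and the article's own remarks make birth weight a plausible consequence of that exposure. The adjusted odds ratio may therefore not be the quantity hypothesised.

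No size or direction can be given from the document. The span of 1.28 to 1.43 around a total odds ratio of 1.35 rests entirely on assumed path strengths, and it collapses to 1.35 if birth weight is unrelated to cancer. The documents do not show that an effect is removed or that a null result becomes more likely, and they do not support dropping gestational age from the primary model. This is an inexpensive improvement in matching the estimate to the hypothesis, not a demonstrated bias.

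**What to change.** Take birth weight out of the primary conditional logistic model for objective 2. Report the model that adds it as a secondary analysis, labelled as a direct-effect estimate. Keep parental age, smoking during pregnancy and gestational age in the primary model, and show the estimate without gestational age as a sensitivity analysis. Settle this before results are seen; the article says under Hypotheses and objectives that the protocol will be updated for deviations.

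The cost is a sentence or two of wording and one or two extra models on variables already planned for. The drawback is that the primary model loses any proxy control for unmeasured confounding that birth weight might give. Comparing it with the secondary model would show how much the estimate depends on that choice.
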